## **10.7. Study cohorts to be evaluated**

### **10.7.1. Total Vaccinated cohort**

The Total Vaccinated Cohort will include all vaccinated subjects for whom data are available. Thus, the total analysis of safety will include all subjects with at least one vaccine administration documented; the total analysis of efficacy will include all subjects with at least one vaccine administration documented and data concerning efficacy endpoint measures are available; the total analysis of immunogenicity will include vaccinated subjects for whom data concerning immunogenicity endpoint measures are available. The Total Vaccinated Cohort analysis will be performed per treatment actually administered.

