### **Study design**

- Experimental design: Phase IIb, two-center, double blind (observer blind, participant blind), randomized (1:1 ratio), controlled trial with two groups.
- Healthy male and female children aged 5 to 17 months will be screened; those determined to be eligible, based on the inclusion and exclusion criteria, will be enrolled in the study.

- Hepatitis B immunization status will be recorded on the CRF at study entry.
- All EPI vaccines given throughout the trial will be recorded in the CRF.
- Route of administration: all vaccines will be administered by the intramuscular route to the left deltoid.
- Each child will be observed for at least 60 minutes after vaccination to evaluate and treat any acute adverse events (AEs).
- There will be a 7-day follow-up period for solicited AEs post-vaccination: Day 0 evaluation will be carried out by the study physician at the study center. Subsequently, trained field workers will visit the children to solicit adverse events (AEs) on days 1 to 6 after each vaccination.
- There will be a 30-day (day of vaccination and 29 subsequent days) follow-up after each vaccine dose for reporting unsolicited symptoms.
- Serious adverse events (SAEs) will be recorded throughout the study period. Prior to vaccination, any SAEs due directly to study procedures will be captured. All SAEs will be captured beginning with the administration of the first dose and ending 12 months after Dose 3 of study vaccines.
- All children will be followed by Active Case Detection (ACD) and Passive Case Detection (PCD) for a period extending to one year post Dose 3, ***and then, under a separate consent, until October 2008 in Kilifi and September 2008 in Korogwe.***

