### **10.7.2. According-to-Protocol (ATP) cohort for analysis of safety**

The ATP cohort for analysis of safety will include all evaluable subjects;

- who have received at least one dose of study vaccine according to their random assignment.
- have sufficient data to perform an analysis of safety (at least one vaccine dose with safety follow-up).
- for whom administration site of study vaccine is per protocol.

- who have not received a vaccine not specified or forbidden in the protocol and for whom elimination criteria were not applied.
- for whom the randomization code has not been broken.
- who meet all eligibility criteria.

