#### **10.7.4. According-to-Protocol (ATP) cohort for analysis of efficacy**

The ATP cohort for analysis of efficacy will include all evaluable subjects (i.e. those meeting all eligibility criteria, complying with the procedures defined in the protocol, with no elimination criteria during the study) for whom data concerning efficacy endpoint measures are available.

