### **10.10.1. Analysis of efficacy**

Analysis of efficacy will be performed on the ATP Cohort for Efficacy and Total Cohort. Vaccine efficacy endpoints:

- time to first/only case of malaria.
- multiple events of malaria.
- parasite prevalence and density.
- hemoglobin values.

will be analyzed according to methods described in Section 10.9.

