**Appendix G Vaccine supplies, packaging and accountability****1. Vaccine and/or other supplies**

GSK Biologicals will supply the following study vaccines, sufficient number of doses to administer to all subjects as described in the present protocol.

- Sufficient doses for 445 recipients of the candidate vaccine RTS,S/AS01E (doses of RTS,S vaccine in monodose vials and doses of AS01E adjuvant in vials).
- Sufficient doses for 445 recipients of Sanofi-Pasteur's Human Diploid Cell Rabies Vaccine

Amended 20 December 2006

At least an additional 3% of their respective amounts of RTS,S/AS01E and Sanofi-Pasteur's Human Diploid Cell Rabies Vaccine will be supplied for replacement in case of breakage, bad storage conditions or any other reason that would make the vaccine unusable (i.e. given by mistake to another subject).

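### The Total Vaccinated Cohort is grouped by vaccine received for efficacy as well as safety, so no efficacy analysis compares all vaccinated children by randomised group; the expected effect is small

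*Protocol*

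**What the plan says.** The trial is "randomized (1:1 ratio), controlled trial with two groups".

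Section 10.7.1 describes the Total Vaccinated Cohort for three purposes in one paragraph. For efficacy, "the total analysis of efficacy will include all subjects with at least one vaccine administration documented and data concerning efficacy endpoint measures are available". The paragraph ends with a rule for the cohort as a whole: "The Total Vaccinated Cohort analysis will be performed per treatment actually administered". There is no separate rule for efficacy.

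Section 10.10.1, on the final analysis, says "Analysis of efficacy will be performed on the ATP Cohort for Efficacy and Total Cohort". Section 10.11.1 names the same two cohorts for the annex analysis. Section 10.7.4 limits the ATP efficacy cohort to evaluable children, that is, "those meeting all eligibility criteria, complying with the procedures defined in the protocol, with no elimination criteria during the study", who have efficacy data.

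Random assignment appears in only one cohort definition, the ATP cohort for safety (10.7.2), as a condition of entry: children "who have received at least one dose of study vaccine according to their random assignment".

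Appendix G, on spare supplies, mentions a dose "given by mistake to another subject" as an example of why a replacement might be needed.

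**The concern.** Grouping by vaccine received is the usual choice for safety, where the question is what happened to children exposed to a product. For efficacy it gives up part of what randomisation provides, because a child who receives the wrong vaccine is moved to the other arm by an event after randomisation. If such children differ in malaria risk from the rest, the comparison is biased in a direction that cannot be known in advance.

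The Total Vaccinated Cohort is the inclusive efficacy analysis in this protocol. Section 10.9.4 even gives it a start of risk time for children who never received Dose 3. It is the natural check on the compliance-selected ATP estimate, and that check is most useful when the children are compared as randomised.

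The protocol is not merely silent here: it prescribes as-treated grouping. An analysis plan that grouped efficacy by randomisation would depart from 10.7.1, so the sentence should be corrected where it stands.

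**Working it through.** **1. The plan's own figures.** Section 10.6.1 assumes attack rates of 36% (control) and 25.2% (vaccine), VE of 30%, 400 evaluable children per group and a two-sided Fisher exact test at 5%. Exact enumeration gives power of 90.2%, against the stated 90%. Expected first episodes are 400 × 0.36 + 400 × 0.252 = 244.8, against the stated 245. Both reproduce, and the grouping rule does not affect them.

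**2. Which efficacy analysis keeps all vaccinated children as randomised?**

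| Cohort | Who is in it | A child given the wrong vaccine |
|---|---|---|
| Total Vaccinated (10.7.1) | at least one documented dose, efficacy data | counted under the vaccine received |
| ATP efficacy (10.7.4) | eligible, compliant, no elimination criterion, efficacy data | expected to be excluded |

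In the first cohort the label can change; in the second the child is expected to be missing. Neither compares all vaccinated children by assigned group.

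**3. How many children?** Inputs: 890 enrolled, 445 per arm (Synopsis). The wrong-box rate is an assumption of 0.5 to 1%, because the protocol gives none.

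- Wrong boxes: 0.005 × 890 = 4.5, and 0.01 × 890 = 8.9.
- Chance that another child's box holds the other vaccine: 445/889 = 0.50.
- Children who change arm: about 2.2 to 4.5, or roughly 2 to 4.
- Average attack rate: (36% + 25.2%)/2 = 30.6%; 890 × 0.306 = 272 first episodes in all.
- Episodes carried by the children who change arm: 2.2 × 0.306 = 0.7, to 4.5 × 0.306 = 1.4, so about 1.

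**4. How far could as-treated grouping mislead?** Take a true VE of 0, an average risk of 36% in each randomised arm of 400, and *m* control children with risk *r* who all received RTS,S/AS01E. Then

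apparent VE = 1 − [(144 + *m r*)/(400 + *m*)] / [(144 − *m r*)/(400 − *m*)].

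| *m* (all one way) | *r* = 18% | *r* = 36% | *r* = 72% |
|---|---|---|---|
| 4 | +1.0% | 0 | −2.0% |
| 5 | +1.2% | 0 | −2.5% |
| 10 | +2.5% | 0 | −5.1% |
| 20 | +4.9% | 0 | −10.6% |

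For *m* = 4 and *r* = 72%: 146.88/404 = 0.3636; 141.12/396 = 0.3564; 1 − 0.3636/0.3564 = −2.0%. There is no bias when the misdosed children have average risk. The rows are deliberately unfavourable: every error goes the same way, and the outer columns give the misdosed children half or double the average risk. The rows for 10 and 20 lie well beyond the count in step 3.

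**5. What would grouping by randomisation cost?** Let *e* be the share of each arm that fully received the other vaccine. Control risk becomes 0.36(1 − *e*) + 0.252*e*, and vaccine risk becomes 0.252(1 − *e*) + 0.36*e*. The rates in step 3, halved, give *e* = 0.25% to 0.5%, which is 1 to 2 children per 400.

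| *e* | Control risk | Vaccine risk | Expected VE | Exact Fisher power |
|---|---|---|---|---|
| 0 | 36.0% | 25.2% | 30.0% | 90.2% |
| 0.25% | 35.973% | 25.227% | 29.9% | 89.9% |
| 0.5% | 35.946% | 25.254% | 29.7% | 89.6% |
| 1.25% (5 per 400) | 35.865% | 25.335% | 29.4% | 88.6% |

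**The case against.** The strongest reply is that this barely matters. The rule governs one of two efficacy cohorts. The trial was sized on evaluable children, and the Glossary ties that term to the ATP analysis, so the sizing is untouched. Boxes carry a unique treatment number for each child, and the number used at first vaccination is recorded (5.3, 6.4.2), which leaves limited room for error. The mention in Appendix G is an example in a supply clause, and erroneous administration in 8.5.2 is one entry in a list of possible contributors to serious events. Neither implies an expected rate. All of this stands, and it is why the point is minor. It does not make as-treated grouping the better choice for an inclusive efficacy analysis.

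A reader might infer three stronger things that the documents do not support:

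- **That the ATP comparison is also as-treated.** The sentence in 10.7.1 does not govern that cohort. A misdosed child would be expected to leave it, so the remaining labels would match randomisation. Its limitation is selection after randomisation.
- **That errors clustered by vaccination day would shift malaria exposure between arms.** Children are invited by area and randomised in order of arrival (6.4.2), so each session mixes both arms from one area and mix-ups would largely exchange similar children. Nothing in the protocol points to one-directional errors across a session.
- **That the lack of an arm for a child with doses of both vaccines is a defect.** That detail is properly left to the Report and Analysis Plan.

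It is also fair to say that the repair would not produce a full intention-to-treat analysis. The total analysis of efficacy would still require efficacy data, and time at risk would still start 14 days after Dose 3, or at Day 75 for children without it (10.9.4).

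**Conclusion.** The point holds in a limited form, at low severity. Section 10.7.1 prescribes grouping by vaccine received for the inclusive efficacy analysis, and the only other efficacy cohort is a compliance-selected subset. No efficacy analysis in the protocol therefore compares all vaccinated children by randomised group.

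On the assumed wrong-box rate, a reasonable expectation is a negligible change in the estimate: about 1 first episode could sit in the other arm. Even 4 errors all in one direction, in children at half or double the average risk, would move an apparent VE by about 1 to 2 percentage points. This rests on the assumed error rate, on 1:1 allocation making about half of wrong boxes harmless for grouping, and on the attack rates in 10.6.1. The ATP reading rests on a wrongly dosed child counting as non-compliant with protocol procedures, which 10.7.4 implies but does not state outright.

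**What to change.** In 10.7.1, limit the sentence on treatment actually administered to safety and immunogenicity. Add that the total analysis of efficacy groups every vaccinated child by the assignment on the randomisation list, with the as-treated efficacy result reported as a sensitivity analysis. Sections 10.10.1 and 10.11.1 can stay as they are, because they refer to the cohort by name.

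The cost is one amended sentence and one additional sensitivity analysis. No new data are needed, since the randomised assignment is already held. If misallocations occur, VE is slightly diluted: 0.1 to 0.3 percentage points at the assumed rate, with exact power moving from 90.2% to between 89.6% and 89.9% in the illustration with 400 per group.

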### **10.7.2. According-to-Protocol (ATP) cohort for analysis of safety**

The ATP cohort for analysis of safety will include all evaluable subjects;

- who have received at least one dose of study vaccine according to their random assignment.
- have sufficient data to perform an analysis of safety (at least one vaccine dose with safety follow-up).
- for whom administration site of study vaccine is per protocol.

- who have not received a vaccine not specified or forbidden in the protocol and for whom elimination criteria were not applied.
- for whom the randomization code has not been broken.
- who meet all eligibility criteria.

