| eTrack                               | GSK's clinical trials tracking tool.                                                                                                                                                                                                                                                                                                                                                                                                                                                                                                                                                                                                                                                                           |
| Evaluable:                           | Meeting all eligibility criteria, complying with the procedures defined in the protocol, and, therefore, included in the according-to-protocol (ATP) analysis (see Sections 4.3, 4.4, and 10.7.2 for details on criteria for evaluability).                                                                                                                                                                                                                                                                                                                                                                                                                                                                    |
| Investigational product:             | A pharmaceutical form of an active ingredient or placebo being tested or used as a reference in a clinical trial, including a product with a marketing authorization when used in a way different from the approved form, or when used for an unapproved indication, or when used to gain further information about an approved use. The investigational products for this study are RTS,S/AS01E and Sanofi-Pasteur's Human Diploid Cell Rabies Vaccine .                                                                                                                                                                                                                                        |

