## **6.5. Method of blinding and breaking the study blind**

Data pertaining to RTS,S/AS01E or rabies vaccine will be collected in a double blinded (observer blinded) manner. 'Double blinded (observer blinded)' means that the vaccine recipient and their parent(s)/guardian(s) as well as those responsible for the evaluation of safety and immunogenicity endpoints will all be unaware which treatment, RTS,S/AS01E or rabies vaccine, was administered to a particular subject. The only study staff aware of the vaccine assignment for RTS,S/AS01E or rabies vaccine will be those responsible for the storage and preparation of vaccines; these staff will play no other role in the study.

Code break envelopes, for each study enrolled subject and associating each treatment number with a specific vaccine, will be kept by the Local Safety Monitors in Kenya and Tanzania as well as by Central Safety at GSK Biologicals, Rixensart in a safe and locked place with no access for unauthorized personnel.

If deemed necessary for reasons such as safety or to guide treatment in a subject exposed to rabies, the relevant Local Safety Monitor together with the GSK Biologicals Central Safety Contact will unblind the specific enrolled subject.

A formal reporting and analysis plan (RAP) will be developed. Once the study is completed and the GSK Biologicals reference database locked, GSK Biologicals will be responsible for initiating the execution of the statistical analysis plan in collaboration with KEMRI, JMP and MVI and breaking the blind.

GSK Biologicals' policy (incorporating ICH E2A guidance, EU Clinical Trial Directive and Federal Regulations) is to unblind any serious adverse event (SAE) report associated with the use of the investigational product, which is unexpected and attributable/suspected, prior to regulatory reporting. The Clinical Safety Physician is responsible for unblinding the treatment assignment in accordance with specified time frames for expedited reporting of SAEs (Refer to Section 8.8).

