#### **10.10.4. Analysis of safety**

##### **10.10.4.1. Secondary safety endpoints**

Safety will be analyzed on the Total Vaccinated Cohort. If the percent of enrolled subjects excluded from the ATP cohort for analysis of safety is more than 5%, a second analysis based on this ATP cohort will be performed to complement the Total Vaccinated Cohort analysis.

Analysis of the occurrence of SAEs will be performed on the Total Vaccinated Cohort. The proportion of subjects with an SAE, classified by the MedDRA preferred term level, reported from study start until Clinic Visit 6 (end of the double-blind phase) will be tabulated with exact 95% CI.

The proportion of subjects reporting an AE (unsolicited) 30 days post each vaccination, classified by the MedDRA preferred term level, reported from study start until the end of the double-blind phase will be tabulated with exact 95% CI.

The percentage of subjects with at least one local adverse event (solicited and unsolicited), with at least one general adverse event (solicited and unsolicited) and with any adverse event during the solicited follow-up period will be tabulated with exact 95% CI after each vaccine dose and overall. The percentage of doses followed by at least one local adverse event (solicited and unsolicited), by at least one general adverse event (solicited and unsolicited) and by any adverse event will be tabulated, overall vaccination course, with exact 95% CI. Similar tables will be generated for Grade 3 events, the relationship of the event to vaccination.

The percentage of subjects reporting each individual solicited local and general adverse event during the solicited follow-up period will be tabulated with exact 95% CI. The percentage of doses followed by each individual solicited local and general adverse event will be tabulated, overall vaccination course, with exact 95% CI. Similar tables will be generated for Grade 3 events, the relationship of the event to vaccination and for fever and temperature in 0.5°C increments.

Biochemistry (ALT and creatinine) and hematology (hemoglobin, WBC, platelets) values that are outside of the reference ranges will be described for Clinic Visit 6 (end of double-blind phase). Frequency distribution of results by toxicity grades will be tabulated by group.

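### The ATP safety cohort excludes children whose code was broken, and the code can be broken because of a suspected vaccine-related SAE, so a supportive safety analysis selects on a safety outcome

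*Protocol*

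**What the plan says.** Section 10.7.2 lists the conditions for the ATP safety cohort. One is that the child must be among those "for whom the randomization code has not been broken". It gives no exception for the reason for the break, its date, or who made it.

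Section 6.5 describes two ways in which treatment can be revealed for one child:

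- The Local Safety Monitor, with the sponsor's central safety contact, may unblind an individual child: "If deemed necessary for reasons such as safety or to guide treatment in a subject exposed to rabies".
- The sponsor's policy "is to unblind any serious adverse event (SAE) report associated with the use of the investigational product, which is unexpected and attributable/suspected". This is done before regulatory reporting, by the sponsor's safety physician.

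Section 10.10.4.1 sets the populations for the safety analysis: "Safety will be analyzed on the Total Vaccinated Cohort". It then adds a condition: "If the percent of enrolled subjects excluded from the ATP cohort for analysis of safety is more than 5%, a second analysis" is carried out on the ATP safety cohort, as a complement to the main one. A separate paragraph of the same section assigns SAE occurrence to the Total Vaccinated Cohort, and section 10.11.2 does the same for the annex analysis. Under section 10.7.1 that cohort includes, for safety, every child with a documented vaccination, and broken codes play no part in it.

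**The concern.** An ATP safety cohort normally excludes children whose handling departed from the protocol in ways that blur the comparison. Here one exclusion can be caused by what the cohort is meant to describe. A suspected reaction leads to unblinding, and unblinding removes the child. The removal covers the whole child, so doses and events that were observed blind go as well.

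The loss need not be equal between groups. Sponsor unblinding requires a suspicion of relatedness, so if one vaccine gives rise to more suspected reactions, that group loses more children from the ATP tables. The ATP analysis is described as a complement to the main one. A complement that leaves out such children by construction cannot add reassurance about them, and a slightly cleaner ATP result could come from the cohort rule alone.

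**Working it through.** **Step 1. Does a safety outcome lead to exclusion?** Setting the sections side by side:

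| Stage | Rule | Where |
|---|---|---|
| Safety event | Unexpected SAE suspected to be related, or another safety reason | 6.5 |
| Consequence | Treatment assignment revealed for that child | 6.5 |
| Cohort rule | A broken code removes the child, with no exception | 10.7.2 |

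Read as written, the answer is yes.

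**Step 2. Which tables are affected?**

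| Output | Population | Affected? |
|---|---|---|
| Main safety analysis | Total Vaccinated Cohort (10.10.4.1) | No |
| SAE occurrence, double-blind phase | Total Vaccinated Cohort (10.10.4.1) | No |
| SAE occurrence, annex | Total Vaccinated Cohort (10.11.2) | No |
| Complementary analysis: solicited, unsolicited, Grade 3 and related AEs | ATP safety cohort, if triggered (10.10.4.1) | Yes |

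Section 8.4 has all adverse events within 30 days of a dose recorded whatever their severity. A suspected reaction in that window could therefore also belong in the unsolicited and relatedness tables, and their ATP versions would lack it.

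**Step 3. When is the complementary analysis run?** The inputs are 890 children to be enrolled (Synopsis) and a trigger of more than 5% excluded (10.10.4.1).

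- 0.05 × 890 = 44.5, so at least 45 children must be excluded, for any mix of reasons.

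**Step 4. How many children could the rule remove?** The protocol does not give the number of code breaks. Let k be that number, assumed to lie between 1 and 10.

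- k = 1: 1/890 = 0.1% of enrolment.
- k = 5: 5/890 = 0.6%.
- k = 10: 10/890 = 1.1%.

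Over this range code breaks could not reach the trigger alone. If the analysis is triggered by other exclusions, and 1 to 5 breaks all fall in one group of about 445, that group's ATP tables lose 1/445 = 0.2% to 5/445 = 1.1% of its children. That is small as a proportion, but these children are selected for suspected reactions.

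The protocol states no figure of its own on this point, so there is none to reproduce.

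**The case against.** The strongest reply is that the events that matter most are already protected. Those that prompt sponsor unblinding are SAEs, and SAE occurrence is assigned to a cohort that keeps every vaccinated child. **This stands.** A reader might infer that the suspected SAEs vanish from the SAE results or appear there as 0%. The protocol specifies no SAE table on the ATP cohort, so that does not follow.

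A second reply is that the complementary analysis may never be run. **This also stands.** A reader might set 890 enrolled against about 800 evaluable, get (890 − 800)/890 = 10.1%, and conclude that the 5% trigger will be passed. But the 800 is the number expected to be evaluable at study end (Synopsis), and the 400 per group is the basis of the efficacy power calculation (10.6.1). Section 10.7.2 asks for only one dose as randomized with safety follow-up, besides its other conditions. A child who later drops out or misses Dose 3 can remain. The 10.1% therefore cannot be taken as the exclusion rate for this cohort.

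A third reply is that 10.7.2 does not say whether unblinding an SAE report centrally counts as a broken code, and that the reporting and analysis plan promised in 6.5 could settle this. **This stands in part.** The wording is open on that route. Individual unblinding for safety reasons, however, is a code break on any reading, and the exclusion itself is fixed in this protocol without an exception.

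**Conclusion.** The point holds as a minor flaw in a supportive analysis. Entry to the ATP safety cohort can depend on a safety outcome, and if that analysis is run its adverse event tables omit the affected children for all doses, including what was observed before unblinding. The main safety analysis and both SAE analyses are not affected.

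The size is unknown but likely to be a handful of children. The 0.1% to 1.1% range rests on an assumed 1 to 10 code breaks. The conclusion assumes that 10.7.2 is applied as written; if central unblinding for regulatory reporting is not treated as a code break, only the individual breaks made for safety reasons remain.

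A reader might also carry the exclusion over to efficacy and immunogenicity, because the glossary entry for evaluable subjects says "see Sections 4.3, 4.4, and 10.7.2 for details on criteria for evaluability". The operative text does not support this. Sections 10.7.3 and 10.7.4 each define evaluable in place, by eligibility, compliance with procedures and absence of elimination criteria. None of these names code break, and section 4.5 does not list it as an elimination criterion.

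**What to change.** Add one sentence to section 10.7.2: the code-break exclusion does not apply when the code was broken because of an adverse event, including sponsor unblinding for regulatory reporting. Keep these children's safety data in the ATP safety cohort and flag events with onset after unblinding, so that a reader can see which were observed with the assignment known. The exclusion can stay for breaks made for other reasons.

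The cost is small: a few unblinded children remain in the cohort, and the flag deals with that. The change concerns an analysis population only. It leaves the unblinding procedures and the care of the children as they are, and it needs no change to the ATP efficacy or immunogenicity cohorts.
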